### Participants

#### Study Population

Patients with communication difficulties, here defined as an impairment in the ability to convey concepts of both verbal and nonverbal form and that the impairment is to such an extent that it causes caregivers to worry that the patient may experience pain and distress without being able to notify them.

#### Inclusion criteria

To be included in the study participants must meet the following criteria: Male or female between 5 and 70 years of age at the time of study inclusion. All participants will be evaluated for ASD diagnosis in accordance with ICD-10 by a clinical psychologist taking into consideration that symptoms of ASD and ID often overlap in low-functioning individuals with, making clear-cut diagnosis difficult [6–8] (Fig. 2). Social Communication Questionnaire [61–63] will be used as part of the diagnostic evaluation. Participants may have cerebral palsy to a degree that compounds the patient’s communication problems. Written informed consent must also be obtained from the participant's legal representative.

**Fig. 2 Fig2:**
[figure not shown]
Trial flow diagram.As the participant cannot give informed consent, it is the legal representative or parent who decides on participation or to withdraw. Screening includes diagnosis of severe or profound ID and fulfilling ASD diagnostic criteria. Assessments will take place at baseline (week 1), end of week 3 and post-treatment

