## Methods

### Study design overview

This is a single centre, controlled, randomized trial with 38 non-verbal participants, testing if HR-guided interventions in suspected painful settings will change the incidence of pain. The study design includes a two-week *pre-intervention*, consisting of continuous HR registering across four potentially painful settings; and an *intervention phase* consisting of formal change in procedure for the identified painful situation (Fig. 1). The interventions are in one of four forms: changes in 1) physiotherapy techniques, 2) preparations for putting on casts, 3) lifting techniques or 4) personal hygiene procedures. HRV and inflammatory cytokines (MCP-1, IL-1RA, IL-8, TGFβ1, and IL-17) are measured at the beginning, midway, and end of the study period to assess change in long-term pain. Participants will be randomly assigned to either an early intervention group or a delayed intervention group in a 1:1 ratio using a computer-generated randomization scheme. This will differentiate the effect of formal change in routine from increased attentiveness due to study participation, and instant changes made when the HR band signify obvious acute pain (such as skin pinched while putting on a cast). Overview over measures and objectives is given in Table 1.

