**Fig. 1 Fig1:**
[figure not shown]
Overview of phases in a clinical study. Abbreviations: HR: heart rate, HRV: heart rate variability, NCPC: Non-communicating Children’s Pain Checklist; NCAPC: Non-Communicating Adult Pain Checklist

**Table 1 Tab1:** Timeline of trial illustrating the timing of different biomarkers and data collection, as well as their corresponding hypothesis

Timepoint	T0		T1		T2	
Nr. Week	1	2	3	4	5	6
Early group	Pre-intervention phase^a^		Change in care procedure			
Delayed group	Pre-intervention phase^a^				Change in care procedure	
Time of samples collected and corresponding hypothesis						
*Primary hypothesis*	HR↑ + context	HR↑ + context	HR↑ + context	HR↑ + context	HR↑ + context	HR↑ + context
*1*^*st*^* Secondary*	HR↑	HR↑	HR↑	HR↑	HR↑	HR↑
	Cytokines			Cytokines		Cytokines
	HRV			HRV		HRV
2^nd^* Secondary*	CU^b^					CU^b^

^a^Registration of HR increases in potentially painful situations in the patient’s everyday life

^b^Caregivers’ rated understanding of the patient as measured by a trial-specific survey, given in Table 4

*Abbreviations*: *TG* Treatment group, *DG* Delayed intervention group; HR↑ = Heart rate increases; Context = Contextual data; Cytokines = MCP-1, IL-1RA, IL-8, TGFβ1, and IL-17; HRV = heart rate variability; metabolites; CU = ^b^Caregiver’s rated understanding

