#### Method of assigning participants to treatment groups

The study design employs an early and a delayed intervention group to distinguish the effects of formal routine changes from increased attentiveness due to study participation and effects of instantaneous changes in care. The early intervention group will start intervention in week three while the delayed group will continue data collection for another two weeks before introducing procedure changes. Patients will be randomly assigned to one of the two groups (Fig. 1) on a 1:1 ratio using a computer-generated randomization scheme.

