#### HRV monitoring of prolonged pain

HRV is a non-invasive measure of parasympathetic nervous system activity [74, 75]. Lower levels of HRV (i.e., reduced parasympathetic nervous system activity) have been associated with both poor somatic and psychiatric health [76, 77]. Like the HR, HRV is calculated continuously through the Polar OH1 armband. Additionally, HRV will be assessed at rest with a portable electrocardiogram (ECG). The ECG will be collected at baseline, after two weeks of intervention in the early group, and at the end of the study period.

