#### Biochemical measurements

We will collect blood and saliva samples to measure biomarkers for long-term pain and stress at baseline, after two weeks of intervention in the early group, and at the end of the study period.

Determinations for assessment of systemic evidence of inflammation include CRP and ferritin [78], as well as Nam [79, 80]. CRP and Nam will be analysed using marker-specific salivary kits. Blood samples will be analysed at Oslo University Hospital for haemoglobin, haematocrit, red blood cell count, white blood cell count, white blood cell differential, platelet count, erythrocyte sedimentation rate, CRP and ferritin.

Pain-related inflammatory biomarkers include MCP-1, IL-1RA, IL-8, TGFβ1, and IL-17 [81–88]. Analyses will be performed at the Department of Clinical Chemistry, Oslo University Hospital, Oslo, Norway, on an Integra 800 instrument following standard protocol Roche Diagnostics, IN, USA; for details of the diagnostics pipeline, please see [name] et al., 2022 [89].

PhD [name] will perform all analysis of inflammatory markers at Oslo University Hospital.

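### The Fig. 2 caption puts the mid-study assessment at the end of week 3; the biomarker and ECG sections and Table 1 put it at the end of week 4, which changes early-arm exposure at the only sample with an unchanged comparator

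*Protocol article*

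**What the plan says.** All references are to the protocol article.

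- **Fig. 2 caption (trial flow diagram):** "Assessments will take place at baseline (week 1), end of week 3 and post-treatment".
- **HRV monitoring of prolonged pain:** "The ECG will be collected at baseline, after two weeks of intervention in the early group, and at the end of the study period".
- **Section on biochemical measurements:** blood and saliva are collected "at baseline, after two weeks of intervention in the early group, and at the end of the study period".
- **Method of assigning participants to treatment groups:** "The early intervention group will start intervention in week three". By the same section, procedures in the other arm change two weeks later.
- **Table 1:** the cytokine and HRV entries stand in the columns for weeks 1, 4 and 6. The delayed group's procedure change begins in week 5.
- **Study design overview:** HRV and cytokines "are measured at the beginning, midway, and end of the study period to assess change in long-term pain".
- **Analysis of secondary objectives:** biomarker difference scores are to be compared between the early and delayed groups. No time point is named for that comparison.

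**The concern.** The caption and the body text cannot both be followed. A site working from the flow diagram would take the middle sample a week before a site working from the biomarker or ECG section.

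The date matters because of what this sample does. The early and delayed arms exist to separate the effect of a formal procedure change from the effects of extra attention and informal adaptation. At baseline neither arm has changed procedure; by the last sample both have. For the cytokines and the resting ECG, only the middle sample has one arm changed and the other not. The between-group analysis names no time point, so the visit schedule alone decides how much exposure is compared. If practice is mixed, one-week and two-week exposures are pooled in the early arm. Samples cannot be re-timed once they are drawn.

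**Working it through.** **Step 1: exposure at the middle sample.** Exposure is the sampling time minus the start of the formal change. Take the earliest start the text allows, the beginning of week 3 for the early arm and of week 5 for the delayed arm.

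| Source | Middle sample | Early arm | Delayed arm |
|---|---|---|---|
| Fig. 2 caption | end of week 3 | 3 − 2 = 1 week | 0 |
| HRV and biochemical sections | two weeks into the early arm's intervention = end of week 4 | 4 − 2 = 2 weeks | 0 |
| Table 1 sampling rows | week 4 | up to 2 weeks | 0 |

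A start later within week three leaves less than one week under the caption, so one week is the maximum. Exposure under the caption is at most 1/2 of that under the body text.

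**Step 2: could the caption mean a different visit?** The pain checklist is scored at the start of the trial, and the caregiver questionnaire at the beginning and end. The biomarker and ECG visit is the only middle assessment the article describes, so the caption must refer to it.

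**Step 3: the article's own effect size.** The sample size section gives a detectable d = 0.84 for a one-sided paired t-test with 38 patients, alpha 0.05 and 80% power; Fig. 3 gives 0.82. The paired test as described does not reproduce either: with n = 38 the detectable d is 0.41. An independent two-sample one-sided t-test with 19 per arm gives 0.822, the Fig. 3 value. That mismatch is a separate matter. Here d = 0.82 serves only as an assumed two-week between-arm effect.

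**Step 4: power if only a fraction f of the two-week effect is present at one week.**

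Power = 1 − F(t₀.₉₅,df ; df, δ), where F is the noncentral t distribution function, df = 2n − 2 and δ = f × 0.82 × √(n/2).

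- n = 19 per arm: df = 36, critical t = 1.688, √(19/2) = 3.082.
- n = 16 per arm: 38 × 0.85 = 32.3, so 32 completers; df = 30, critical t = 1.697, √(16/2) = 2.828.

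| Sampling and accrual | f | d | δ (19) | Power, 19 per arm | δ (16) | Power, 16 per arm |
|---|---|---|---|---|---|---|
| End of week 4 | 1 | 0.82 | 2.527 | 80% | 2.319 | 73% |
| End of week 3, linear | 1/2 | 0.41 | 1.264 | 34% | 1.160 | 31% |
| End of week 3, two thirds present | 2/3 | 0.547 | 1.685 | 50% | 1.546 | 45% |
| End of week 3, three quarters present | 3/4 | 0.615 | 1.896 | 59% | 1.739 | 52% |

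**Step 5: plausibility of the fractions.** If the effect approaches a plateau with half-life h weeks, then f = (1 − 0.5^(1/h)) / (1 − 0.5^(2/h)) = 1 / (1 + 0.5^(1/h)). For h = 0.5 this is 1/1.25 = 0.80; for h = 1 it is 1/1.5 = 0.67; for h = 4 it is 1/1.841 = 0.54. The half-lives are assumptions; the document gives no time course for cytokines or HRV.

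The t-test stands in for whatever between-group test is used. The analysis section names a Wilcoxon signed-rank test, for which these figures are only a guide.

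**The case against.** The strongest reply is that this is one caption against three concordant statements, so a careful reader can see which date was meant, and that it touches one secondary hypothesis. Both parts are true. They limit the size of the point but do not remove it: the caption belongs to the flow diagram, which staff may well work from, and nothing in the article says which statement governs.

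Several stronger readings are tempting, and the document does not support them.

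- **Table 1's T1 heading as a further conflicting date.** In the extracted text T1 appears above week 3. The heading row is most likely a flattened row of two-week cells: T0, T1 and T2 each precede a blank, and the two-week pre-intervention phase also appears above week 1 alone. Read literally, T2 would be week 5, yet the last samples stand in week 6. Table 1 agrees with the body text.
- **The word midway as the end of week 3.** It is a loose label for the second of three samples and settles nothing.
- **No other untreated comparison for any outcome.** Armband HR and HRV are recorded continuously, so for them all of weeks 3 and 4 has an unchanged comparator, whatever the caption says.
- **An effect that is certainly halved.** Only exposure time is. The effect halves only under linear accrual.
- **A middle sample scheduled after the delayed arm's own change.** Table 1 puts the sample in week 4 and that change in week 5. A late draw is a possibility to guard against, not something the schedule prescribes.
- **Damage to the primary analysis.** That analysis compares types of care situation on HR spike counts and uses no middle biomarker sample.

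**Conclusion.** The inconsistency is real and unresolved in the article. The Fig. 2 caption conflicts with the HRV section, the biochemical section and Table 1's sampling rows on when the middle sample is taken. For cytokines and resting-ECG HRV that sample carries the randomised early-versus-delayed comparison under secondary hypothesis 1.

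What follows from the document alone is that sampling at the end of week 3 reduces early-arm exposure from two weeks to at most one. The loss of power is conditional on an assumed two-week effect of d = 0.82, a one-sided 5% independent t-test and an assumed accrual pattern. Across the three patterns tabulated, power at one week is about 34% to 59% with 19 per arm, against 80% at two weeks, and about 31% to 52% with 16 per arm, against 73%. Faster accrual would make the loss smaller. The point is narrow in scope but more than clerical.

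**What to change.** 1. Reconcile the Fig. 2 caption with Table 1, the HRV section and the biochemical section, so that one T1 applies to blood, saliva and resting ECG in both arms. The body text and Table 1 already agree on the end of week 4. The Table 1 heading needs no change.
2. State that T1 is completed before the formal procedure change begins in the delayed arm.
3. In the analysis of secondary objectives, name T1 as the time point of the early-versus-delayed biomarker comparison.

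The cost is a corrected caption and two added sentences, with no extra visit or sample. It should be done before further middle samples are drawn. If any have already been taken, record the actual date of each relative to the start of the change.

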#### Exclusion criteria

Not living in a care home with round-the-clock staff for at least five days a week; or not attending one-to-one staffed school/day-care at least five days a week. Having any ongoing infection with a C-reactive protein (CRP) > 20 or any type of cancer with ongoing chemotherapy.

#### Sample size

There are various approaches for calculating sample size [64]. Here we have decided to design the study to reliably detect our effect size of interest. We will recruit 38 patients, allowing for a dropout of 15%. With 38 patients, a one-sided paired samples t-test can reliably detect (80% power) an effect size of *d* = 0.84, alpha = 0.05 (Fig. 3). We have chosen a one-sided test as we have a directional hypothesis. This is a realistic effect size of interest given that heart rate increases in response to stressors are associated with effect sizes larger than *d* = 1 [65].

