**Methods:**

We will recruit 38 non-communicative patients with autism and ID residing in care homes. *Assessments*: HR is measured continuously to identify acutely painful situations. HR variability and pain-related cytokines (MCP-1, IL-1RA, IL-8, TGFβ1, and IL-17) are collected as measures of long-term pain. Caregivers will be asked to what degree they observe pain in their patients and how well they believe they understand their patient’s expressions of emotion and pain. *Pre-intervention:* HR is measured 8 h/day over 2 weeks to identify potentially painful situations across four settings: physiotherapy, cast use, lifting, and personal hygiene. *Intervention:* Changes in procedures for identified painful situations are in the form of changes in 1) physiotherapy techniques, 2) preparations for putting on casts, 3) lifting techniques or 4) personal hygiene procedures. *Design:* Nineteen patients will start intervention in week 3 while 19 patients will continue data collection for another 2 weeks before procedure changes are introduced. This is done to distinguish between specific effects of changes in procedures and non-specific effects, such as caregivers increased attention.

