**Fig. 3 Fig3:**
[figure not shown]
A power contour plot. Power analysis suggests that a paired samples t-test including 38 participants will reliably detect (power = 80%) an effect size of 0.82, or higher. Statistical power is also shown by assuming smaller or larger hypothetical effect sizes. Analysis and visualisation were performed using the ‘jpower’ JAMOVI module: https://github.com/richarddmorey/jpower

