## Discussion

In this randomized blinded controlled trial, we aim to study HR to improve communication between patient and caregiver. This clinical study of HR-informed intervention represents an important contribution to the research and practice of developmental disabilities and communication difficulties. Studies on patients with limited communicative abilities are lacking (Table 4). Existing studies investigating severely limited communicative abilities are small and mainly descriptive. Larger studies on technologies for patients with communication disability exclude the most severely debilitated patients. Furthermore, considerable heterogeneity of participant level of communication disability makes for less clinically relevant findings. In the present study we strive to correct this.

**Table 4 Tab4:** Methodological advances of current trial relative to past sensor-technology intervention trials among patients with communication difficulties

Limitations in literature^a^	Current study features
Few controlled trials	Randomized controlled design
Small sample sized/insufficient power/case studies	A sample of 38 patients allowing us to detect an 0.80 effect size
Absence of studies using comparator interventions	Controlling for effect of study participation by including a group with delayed intervention
Exclusion of most vulnerable patients	Inclusion of profoundly disabled patients
Lack of standardized measures and biomarkers	HR, HRV and biochemical biomarkers in blood
No adherence data	Routine signing of protocol by secondary participants to measure adherence
Considerable heterogeneity of participants regarding type and level of communication need	Patients with ID ranging from severe to profound and ranging from ambulant to wheelchair user, loss of eyesight and hearing

^a^Based on published reviews [29, 96], and review of studies on PubMed and Google Scholar using the phrases “sensor-technology intervention intellectual disability” and “technology intervention communication difficulties”

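### The stated detectable effects (d = 0.84 in the text, 0.82 under Fig. 3) do not reproduce for the one-sided paired t-test named, which detects d = 0.41 with 38 patients and d = 0.45 with about 32 completers

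*Protocol article*

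**What the plan says.** All statements are in the protocol article.

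- **Sample size, recruitment target:** "We will recruit 38 patients, allowing for a dropout of 15" per cent.
- **Sample size, detectable effect:** "With 38 patients, a one-sided paired samples t-test can reliably detect (80% power) an effect size of" d = "0.84, alpha = 0.05 (Fig. 3"). The section justifies the one-sided test by a directional hypothesis. It calls the effect realistic because heart rate responses to stressors are associated with effects above d = 1.
- **Fig. 3 caption:** "a paired samples t-test including 38 participants will reliably detect (power = 80%) an effect size of 0.82, or higher".
- **Discussion, Table 4:** "A sample of 38 patients allowing us to detect an 0.80 effect size". No test, alpha or power is given there.
- **Analysis of primary objectives:** a within-patient comparison of mean heart rate spike counts between two kinds of situation. It uses a one-tailed paired t-test, or the Wilcoxon signed-rank test if Shapiro–Wilk indicates non-normality.
- **Abstract, Methods:** "Nineteen patients will start intervention in week 3 while 19 patients will continue data collection for another 2 weeks", so the arms are 19 and 19.
- **Replacement of participants:** withdrawn participants are not replaced.

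**The concern.** Sample size, alpha, sidedness, power and test are all stated, so the detectable effect has a single value. The document nevertheless gives 0.84 and 0.82 for the same test and the same 38 patients, with a third figure in Table 4. For a paired test of this size, an effect above 0.8 at only 80% power also looks far too large.

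This is the only sample-size justification in the article, and the section says the study was designed around its effect size of interest. If the figure does not belong to the named test, the reader does not know how sensitive the primary analysis is. The reader also cannot tell whether the figure was meant for some other comparison. In addition, a 15% dropout allowance is announced, yet the detectable effect is quoted for the full 38.

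**Working it through.** **Inputs.** n = 38, dropout 15%, one-sided paired t-test, alpha 0.05 and power 80% (Sample size); arms of 19 and 19 (Abstract). Expected completers: 38 × 0.85 = 32.3, about 32, or 16 per arm.

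**Formulas (exact noncentral t).**
- Paired: df = n − 1, noncentrality = d × √n, where d is the mean difference divided by the SD of the differences.
- Two groups of m: df = 2m − 2, noncentrality = d × √(m/2).
- Power = P(noncentral t > one-sided 5% critical value). Solve for d at power 0.80.

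**Step 1. The plan's own figure, as the plan describes it.** For n = 38, df = 37 and the critical value is 1.687. Power of 80% needs a noncentrality of 2.533, so d = 2.533 / √38 = 0.411. The normal approximation agrees: (1.645 + 0.842) / √38 = 0.403. The stated 0.84 is about twice this (0.84 / 0.411 = 2.04).

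**Step 2. The same test on completers.** For n = 32, the critical value is 1.696 and the noncentrality needed is 2.543, so d = 2.543 / √32 = 0.449.

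**Step 3. Power of the paired test at the stated effects.**

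| d | 38 pairs | 32 pairs |
|---|---|---|
| 0.84 | 99.97% | 99.87% |
| 0.82 | 99.95% | 99.81% |
| 0.80 | 99.93% | 99.73% |

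Eleven pairs already give 82.8% power at d = 0.84.

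**Step 4. Does another paired variant give 0.80 to 0.84?** Detectable d at 80% power and alpha 0.05:

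| Pairs | One-sided | Two-sided |
|---|---|---|
| 38 | 0.411 | 0.467 |
| 32 | 0.449 | 0.511 |
| 19 | 0.593 | 0.680 |
| 16 | 0.652 | 0.749 |

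None reaches 0.80.

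**Step 5. Could d be scaled by the SD of single measurements instead?** With equal SDs and within-patient correlation r, that d equals the paired d times √(2(1 − r)). To turn 0.411 into 0.82 the factor must be 0.82 / 0.411 = 1.995. Then 1 − r = 1.995² / 2 = 1.99 and r = −0.99. For 0.84 the factor is 2.04, which would need r below −1. A different scaling does not explain the figures.

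**Step 6. A two-group calculation.** One-sided alpha 0.05, 80% power:
- 19 per arm: noncentrality needed 2.5345, so d = 2.5345 / √9.5 = 0.822. This is the Fig. 3 value to two decimals.
- Power with 19 per arm: 81.5% at 0.84, 79.8% at 0.82, 78.1% at 0.80. So 0.84 and 0.80 are not exact solutions. With 18 per arm the solution is 0.846.
- 16 per arm (completers): d = 0.900, with power 75.1% at 0.84, 73.3% at 0.82 and 71.4% at 0.80.

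**Step 7. The dropout allowance.** 32 / 0.85 = 37.6, which rounds up to 38. The total is therefore compatible with 32 completers inflated for dropout. The text and the caption still quote their effects for 38, and no figure is given for 32.

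**The case against.** The strongest defence is that nothing is lost. The primary analysis is the paired test, and for that test the stated effects understate sensitivity. Even with 32 completers, power at d = 0.80 is 99.7%. No sample size or analysis changes. This stands, and it limits the point to correcting a stated figure.

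Other parts of the defence also stand:

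- **Table 4 is weak evidence.** It names no test, alpha or power, may be a rounding, and is literally true of the paired test. It counts as an inconsistency to tidy, not as a further wrong result for the same test.
- **The cause is not shown.** A reader might infer from the 0.822 match that the wrong design was entered in the software. The software inputs are not given, and 19 per arm reproduces neither 0.84 nor 0.80. The match is suggestive only.
- **Dropout may be in the total.** A reader might infer that the 15% was never applied. Since 32 / 0.85 rounds up to 38, that cannot be said. What can be said is that the quoted effects are not for completers.
- **The randomised comparison carries no power claim.** A reader might infer that the trial is underpowered for early versus delayed intervention. That comparison serves a secondary hypothesis, the protocol names a Wilcoxon test for it, and no expected biomarker effect is stated. The documents do not support the inference.

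The defence does not rescue the numbers. The Sample size section fixes every input, those inputs give 0.41, and the text and the Fig. 3 caption disagree about the same test.

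**Conclusion.** The point holds as an error in a stated figure. For the one-sided paired t-test with alpha 0.05 and 80% power, the detectable effect is d = 0.41 with 38 pairs and d = 0.45 with 32. The stated 0.84 and 0.82 are roughly twice the value for 38 and contradict each other, and Table 4 adds 0.80 with no test attached. The direction is conservative for the primary analysis.

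The result assumes that d is the mean difference over the SD of the differences, that every patient counted contributes one pair, and that the t-test branch applies. Under the Wilcoxon signed-rank branch the values are approximations. If patients with no suitable situation provide no pair, the detectable effect is larger than 0.45. How many such patients to expect is not stated. The two-group figures (0.822 with 19 per arm, 0.90 with 16) are context for where 0.82 may have come from. They do not show a shortfall in the trial.

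**What to change.** Give one consistent figure in the Sample size section, the Fig. 3 caption and Table 4: for the primary one-sided paired t-test (alpha 0.05, 80% power), d = 0.45 with 32 completers, or 0.41 if all 38 provide a pair. Add that the detectable effect is larger if patients without a suitable situation contribute no pair. State whether 38 is 32 inflated for 15% dropout. Redraw Fig. 3 for the test that its caption names.

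If 0.80 to 0.84 was meant for the randomised early-versus-delayed comparison, say so and restate it on completers: about d = 0.90 one-sided with 16 per arm, as a t-test approximation to the Wilcoxon test named for that comparison.

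The cost is a text correction in three places and one redrawn figure. No extra patients and no change of design or analysis are needed.
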